### 2.4. Interventional therapy and intraoperative evaluation

Angiography of 4 branches of the whole brain (bilateral common carotid arteries and bilateral vertebral arteries) will be performed to evaluate the primary compensation of the diseased vascular area (circle of Willis compensation: whether the posterior and/or anterior communicating arteries are open). The operation then begins with the use of an embolus protection device. After carotid artery occlusion is expanded by a percutaneous transluminal angioplasty balloon, the catheter will be guided through the internal carotid artery occlusion segment, and intracranial vascular thrombectomy and recanalization will be performed using classical thrombectomy techniques. After successful opening of the occluded vessel or thrombus retrieval, observation will be performed for 30 minutes, and common carotid angiography (lesion vessel assessment angiography) will be repeated to assess the extent, stability, and changes in stenosis at the beginning of the internal carotid artery, in parallel with DynaCT (to confirm the presence of intracranial hemorrhage or contrast spillage). Finally, the next procedural step (whether to place a carotid stent and/or apply antiplatelet agents) will be performed according to the treatment plan decision maker’s instructions.

### 2.5. Treatment plan recommendation and determination

Three surgical options are currently available. Stent placement + immediate normal application of antiplatelet drugs; Stent placement + delayed application of antiplatelet drugs; and no stent placement. “Immediate normal antiplatelet medication” refers to an intravenous tirofiban loading dose before stent placement and continuous intravenous pumping (calculated by kilogram of body weight according to the instructions) until 24 to 48 hours after surgery, followed by aspirin (100 mg), clopidogrel (75 mg), and oral quaque die. Delayed application of antiplatelet drugs means that 24 to 48 hours after surgery, when the condition is stable, as indicated by CT review, aspirin (100 mg) + clopidogrel (75 mg), and oral quaque die will be administered.

The ECASES assessor, a nonsurgical participant, will evaluate each subject (study or control group) according to the ECASES scoring rules (see below) and make ECASES treatment recommendations to the protocol decision maker; the surgeon and their assistant will evaluate and discuss each subject (study or control group) based on their experience and make treatment recommendations to the protocol decision maker. The ECASES assessor and surgical participants will be unaware of their respective treatment recommendations, and the decision maker will select a treatment plan based on subject grouping (ECASES recommendations for the study group/operator’s experience for the control group) and inform the operators of the finalized treatment plan for the next operation; however, they will not inform the operator of the source of the regimen (derived from the ECASES system or operator’s experience) and the subject subgroup.

### 2.6. ECASES

ECASES is divided into 2 risk scoring systems (bleeding risk score and ischemic risk score) and a decision recommendation system that weighs the patient’s bleeding and ischemic risks, resulting in an individualized treatment recommendation for stent placement.

1. The bleeding risk of patients is assessed based on the intraoperative DynaCT results and DWI sequence results on preoperative MRI examinations. Bleeding risk is scored as 0, 1, 2, or 3 (Table 1), with red, yellow, and blue representing high to low bleeding risk grading.

**Table 1 T1:**
[figure not shown]
Risk score for intracranial hemorrhage.

2. The ischemic risk of patients will be assessed based on the primary vascular substitution (anterior communicating artery/posterior communicating artery) and intraoperative observation of the lesion vessels after 30 minutes of assessment angiography. Ischemic risk scores of 0, 1, 2, or 3 are assigned as shown in Table 2; red, yellow, blue, and green represent ischemic risk graded from high to low.

**Table 2 T2:**
[figure not shown]
Risk score for intracranial ischemia.

3. Finally, according to the bleeding and ischemic risk assessments in Tables 1 and 2, recommendations will be made for stent placement and subsequent antiplatelet drug therapy. The color grade of bleeding risk will be first considered, then the ischemic risk will be considered, and finally, the recommendation will be given (Table 3).

**Table 3 T3:**

Individualized stent recommendations.

### 2.7. Postoperative evaluation and patient follow-up

1)Imaging evaluation and follow-up.•CT: 3 planned CT examinations will be performed on the first, third, and 7th to 14th day after surgery. Additionally, CT examinations will be performed at any time according to the disease condition to evaluate intracranial hemorrhage and cerebral edema.•MRI: A planned MRI examination will be performed on the 3rd to 7th days after surgery, and examinations will be performed at any time according to the disease condition to evaluate new cerebral infarction and other conditions.•Vascular imaging examination: 2 planned CTA, MRA, and/or DSA examinations will be performed on the 90th day, 7 to 14 days after the operation, and at any time according to the disease condition to evaluate the reocclusion of the responsible vessels.2)Neurological function assessment and follow-up.

Patients will undergo follow-up evaluation on days 1, 7, 30, and 90 after surgery, and the NIHSS and mRS scores will be assessed.

### 2.8. Study outcomes

Primary outcome: Neurological functional status at 90 days postoperatively

Patient neurological functional status will be assessed by mRS and NIHSS scores.

Secondary outcomes.

Changes in neurological function are classified as improved (postoperative NIHSS score decrease ≥ 4 points compared with preoperative), worsened (postoperative NIHSS score increase ≥ 4 points compared with preoperative), or stable (postoperative NIHSS score change < 4 points).Hemorrhage events: For the classification of bleeding events, we refer to ECASS II.^[9]^ Hemorrhagic events were classified according to the clinical and CT criteria. Hemorrhagic infarction 1 (HI1) was defined as small petechiae along the margins of the infarct, and hemorrhagic infarction 2 (HI2) as confluent petechiae within the infarcted area but no space-occupying effect.

parenchymal hemorrhage (PH1) as blood clots in 30% or less of the infarcted area with some slight space-occupying effect, and parenchymal hemorrhage (PH2) as blood clots in more than 30% of the infarcted area with a substantial space-occupying effect. Symptomatic intracranial hemorrhage was defined as blood at any site in the brain on the CT scan (as assessed by the CT reading panel, independent of the assessment by the investigator), documentation by the investigator of clinical deterioration, adverse events indicating clinical worsening (e.g., drowsiness, increase of hemiparesis), or a decrease in the NIHSS score of 4 or more points.

Cerebral edema: According to postoperative CT results, edema is classified into 4 conditions: no edema, mild edema (focal edema up to one-third of the hemisphere), moderate edema (focal edema greater than one-third of the hemisphere), and severe edema (edema with midline shift).^[10]^ Signs of focal edema are defined as narrowing of the cerebrospinal fluid space, for example, effacement of the cortical sulci or ventricular compression.^[11]^Modified treatment in cerebral infarction (mTICI) grading: The mTICI grading will be assessed based on DSA of the responsible vessel at the end of the procedure to evaluate the effectiveness of surgical revascularization.New cerebral infarction: Postoperative MRI-DWI sequences showed a new cerebral infarction (compared with the preoperative).Reocclusion of the responsible vessel: A responsible artery with an immediate postoperative mTICI classification ≥ 2b and a CTA, MRI, and/or DSA examination within 90 days postoperatively, suggesting artery reocclusion, will be defined as reocclusion of the responsible vessel.

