1)Inclusion criteria.•Age 18–80 years old, regardless of sex.•Preoperative National Institutes of Health Stroke Scale (NIHSS) score ≥ 6.•An Alberta Stroke Program Early Computed Tomography Score (ASPECTS) ≥ 6 based on magnetic resonance imaging diffusion-weighted imaging (MRI-DWI) sequences.•The time from onset to the expected start of endovascular treatment is ≤ 24 hours, with patients between 6 and 16 hours meeting the inclusion criteria for the DAWN study and the DEFUSE 3 study, and patients between 16 and 24 hours meeting the inclusion criteria for the DAWN study.•Pre-stroke modified Rankin Scale (mRS) score of 0–1.•Life expectancy ≥ 2 years.•Patients and their families agree to the endovascular treatment and study protocol and sign an informed consent form.2)Exclusion criteria.•Patients with combined intracranial hemorrhage confirmed by CT or MRI.•Patients with a combination of severe renal insufficiency (creatinine level > 264 µmol/L), respiratory and circulatory instability, severe coagulation dysfunction (international normalized ratio > 3.0, or partial thromboplastin time more than 3 times the normal value), and other contraindications to interventional procedures.•Patients with preexisting neurological(pre-stroke mRS score ≥ 2, stroke attack with epilepsy, combined with intracranial tumors) or psychiatric disorders could confound the results.•Uncontrollable hypertension is defined as a systolic blood pressure > 185 mm Hg and diastolic blood pressure > 110 mm Hg.•Platelet count < 50,000/µL.•Blood glucose < 2.78 mmol/L or > 22.20 mmol/L.•Patients who cannot undergo cranial MRI.•Patients deemed unsuitable for study participation by other investigators.3)Exclusion and discontinuation criteria: Patients may withdraw at any stage of the study.•Voluntary withdrawal, where informed consent is withdrawn, and patients are free to withdraw from the study at any time without prejudice to subsequent treatment.•Missed patient visits.•Any safety reasons (adverse events) as perceived by investigators.•Other cases where researchers decide whether it is appropriate for patients to withdraw from the study.4)Preoperative evaluation.•General information: Age, sex, time of onset, past medical history, and stroke risk factors, including blood pressure, blood glucose, blood count, coagulation series, and electrocardiogram.•Neurological function assessment: NIHSS and mRS scores will be used as tools for neurological function evaluation and completed by senior physicians.•Imaging evaluation: All patients undergo preoperative cranial CT to exclude intracranial hemorrhage and massive cerebral infarction. All patients will undergo cranial MRI to clarify the diagnosis and extent of acute cerebral infarction and will then be scored based on MRI-DWI sequences with reference to the ASPECTS scoring system. The presence of large infarcts in the basal ganglia area (large infarcts: >2/3 of the basal ganglia area) will also be assessed. All the patients will undergo MRA, CTA, and/or DSA to confirm the presence of atherosclerotic carotid occlusion. In some patients (6–24 hours after onset), CT perfusion imaging or nuclear perfusion imaging will be performed to assess the semidark bands.

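### Any hemorrhage on postoperative CT counts as an event, including bleeding already visible before the arms diverge, which dilutes the risk ratio and costs precision without biasing the risk difference

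*Protocol article*

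**What the plan says.** All references are to the protocol article.

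- **Before surgery (2.2).** An exclusion criterion reads "Patients with combined intracranial hemorrhage confirmed by CT or MRI", and the imaging evaluation places the CT check before the operation. Bleeding during the procedure is therefore not excluded.
- **During surgery (2.4).** After balloon dilation, thrombectomy and 30 minutes of observation, angiography is repeated "in parallel with DynaCT (to confirm the presence of intracranial hemorrhage or contrast spillage"). Only then does the text say that "the next procedural step (whether to place a carotid stent and/or apply antiplatelet agents) will be performed according to the treatment plan" decision maker's instructions. Up to that point both arms are handled alike.
- **Use of the scan (2.5, 2.6).** "The bleeding risk of patients is assessed based on the intraoperative DynaCT results and DWI sequence results on preoperative MRI examinations". Section 2.5 has the ECASES assessor score every subject in both groups.
- **Outcome scans (2.7).** "3 planned CT examinations will be performed on the first, third, and 7th to 14th day after surgery", and further "CT examinations will be performed at any time according to the disease condition to evaluate intracranial hemorrhage and cerebral edema".
- **Outcome definition (2.8).** "Hemorrhagic events were classified according to the clinical and CT criteria", with grades HI1, HI2, PH1 and PH2. The imaging element of symptomatic hemorrhage is "blood at any site in the brain on the CT scan". Neither refers to an earlier scan. In the same section, NIHSS change and new infarction are both measured against the preoperative state.
- **Status.** Hemorrhage is listed as a secondary outcome. The Introduction presents intracranial hemorrhage as the main harm that stenting with antiplatelet drugs may bring.

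**The concern.** The two strategies can differ only in what happens after the DynaCT. A patient who bled during angioplasty or thrombectomy, with blood still visible on the day 1 CT, is an any-hemorrhage event in either arm under either plan. The same finding is an input to the ECASES bleeding score and an event in the outcome used to judge ECASES.

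Events that the strategy cannot influence add the same expected amount to both arms. They raise both event rates, bring the ratio of the rates nearer to 1 and add variance. In a trial of about 100 patients per arm, an increase or a reduction in bleeding due to the decision becomes harder to see.

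**Working it through.** The plan states no expected hemorrhage rate and no power for hemorrhage, so there is no figure of its own to reproduce.

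**Inputs**
- Evaluable patients per arm: 101 with 5% loss (section 2.11), 101 × 0.95 = 95.95, taken as 96.
- Two-sided 5% level (section 2.12), critical value 1.96.
- *b*, the share with bleeding already on DynaCT: not in the document. Assumed 2% to 20%.
- New-bleed rates among patients without earlier bleeding: not in the document. Assumed 20% in control and 10% in the study group; two other pairs are tried below.
- Simplifications: the outcome is any versus none, every earlier bleed is still visible on a postoperative CT, and worsening of an earlier bleed is ignored.

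**Formulas**
- As written: rate = *b* + (1 − *b*)*p*.
- New bleeding only, all randomized patients in the denominator: rate = (1 − *b*)*p*.
- Risk difference under both: *d* = (1 − *b*)(0.20 − 0.10).
- SE = √[(p₁(1 − p₁) + p₂(1 − p₂))/96]; power = Φ(*d*/SE − 1.96).

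**Worked case, *b* = 15%.** As written: 0.15 + 0.85 × 0.20 = 32.0% versus 0.15 + 0.85 × 0.10 = 23.5%. SE = √[(0.2176 + 0.1798)/96] = 0.0643, power = Φ(0.085/0.0643 − 1.96) = 26%. New only: 17.0% versus 8.5%, SE = √[(0.1411 + 0.0778)/96] = 0.0477, power = 43%.

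| *b* | As written | RR | Power | New only | RR | Power | Variance ratio |
|---|---|---|---|---|---|---|---|
| 2% | 21.6% vs 11.8% | 0.55 | 45% | 19.6% vs 9.8% | 0.50 | 49% | 1.11 |
| 5% | 24.0% vs 14.5% | 0.60 | 39% | 19.0% vs 9.5% | 0.50 | 48% | 1.28 |
| 10% | 28.0% vs 19.0% | 0.68 | 32% | 18.0% vs 9.0% | 0.50 | 45% | 1.55 |
| 15% | 32.0% vs 23.5% | 0.73 | 26% | 17.0% vs 8.5% | 0.50 | 43% | 1.82 |
| 20% | 36.0% vs 28.0% | 0.78 | 22% | 16.0% vs 8.0% | 0.50 | 40% | 2.08 |

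In each row the risk difference is the same on both sides (9.8, 9.5, 9.0, 8.5 and 8.0 points).

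**Other assumed rates, *b* = 20%, same formulas.** For 30% versus 15%: RR 0.73 instead of 0.50, power 41% instead of 59%. For 15% versus 5%: RR 0.75 instead of 0.33, power 24% instead of 54%.

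**Does stratifying recover the precision?** In this model every patient in the bleeding stratum is an event in both arms, so that stratum contributes no variance. The stratified risk difference on total hemorrhage then has variance (1 − *b*)(0.16 + 0.09)/96. At *b* = 10% this is 0.225/96, SE 0.0484, power Φ(0.09/0.0484 − 1.96) = 46%. At *b* = 20% it is 0.200/96, SE 0.0456, power 42%. Stratification therefore restores the precision of the risk difference while every event is kept. It does not restore a pooled risk ratio, because the bleeding stratum still contributes a ratio of 1; the stratum results or a new-or-worse comparison are needed for that.

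**The case against.** **No bias, and a legitimate endpoint.** Earlier bleeding is balanced in expectation, and total postoperative hemorrhage by intention to treat is a valid outcome. This stands. A reader might infer that one strategy is systematically favored, or that the trial's main safety endpoint is compromised. The document supports neither: the risk difference is unchanged, and hemorrhage is listed as secondary with no outcome named as the main safety endpoint.

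**Unknown share.** Nothing in the document gives *b*. At 2% the loss is four points of power, and at zero there is none. Even new-only counting reaches at most 49% power here, so neither version is well powered at these rates. This also stands.

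**Grades and symptoms.** Section 2.8 grades hemorrhage and defines symptomatic hemorrhage separately. A comparison across grades would register a severe bleed after earlier petechiae, so the figures apply to an any/none comparison only. For symptomatic hemorrhage the dilution is weaker if clinical worsening is also required; the elements in section 2.8 are joined by an or, which leaves that unclear.

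**DynaCT as reference.** Replacing the outcome with new bleeding might look like the obvious remedy, but the text does not support it as a sole outcome. Section 2.4 has DynaCT look for blood or contrast, the visible text assigns no HI or PH grade on it, and the Discussion links contrast extravasation to hemorrhage. Suppose, by assumption, 5% have true earlier blood, 15% have contrast with later bleeding of 40% versus 20%, and 80% are clean with 20% versus 10%. Total hemorrhage is 0.05 + 0.06 + 0.16 = 27% versus 0.05 + 0.03 + 0.08 = 16%, power 46%. If, at worst, every contrast-then-bleed case is called pre-existing, this becomes 16% versus 8%, power 40%. Real events would be lost.

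**Condensed article.** Reading instructions may exist elsewhere, and Tables 1 and 3 cannot be seen. But section 2.8 spells out the hemorrhage definition at length and gives comparators to neighboring outcomes, so the definition as printed is open to comment.

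**Conclusion.** The point holds in a limited form. As printed, section 2.8 counts bleeding that was already visible before the assigned plan could act, provided it persists to a postoperative CT. The consequence is dilution of the risk ratio and loss of precision for any hemorrhage, a secondary outcome that is also the central harm in the trial's rationale.

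At assumed rates of 20% versus 10%, the loss runs from negligible at a 2% share to roughly half the power at 20%, where the variance is about doubled. These sizes rest on the assumed rates, the unknown share, an any/none analysis, full persistence of earlier blood, and no worsening of earlier bleeds. The change is worth making because the scan is already taken and, under section 2.5, already scored in both arms.

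**What to change.** In section 2.8, and in the analysis plan:

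1. Keep total postoperative hemorrhage, by grade, as an outcome.
2. Record the DynaCT result as clean, contrast or high density, or hemorrhage, for every patient in both arms, before the plan is disclosed. Both arms have been handled alike up to then, so the strategy cannot affect this variable.
3. Compare hemorrhage between arms stratified by, or adjusted for, that result, and show the results by stratum.
4. Add a comparison of hemorrhage that is new or worse than on the DynaCT. Density on DynaCT that is not clearly read as blood does not count as pre-existing hemorrhage, so that a later true bleed at a contrast site is still an event.

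The cost is one form field, one more analysis and some misclassification of contrast versus blood. No treatment, visit or scan changes.

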**Study outcomes::**

Primary outcome: Neurological functional status (modified Rankin Scale and National Institutes of Health Stroke Scale scores) of patients 90 days postoperatively. Secondary outcomes: neurological function changes, hemorrhage events, cerebral edema, postoperative modified treatment in cerebral infarction grade, new cerebral infarction, and reocclusion of responsible vessels.

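### The NIHSS element of the symptomatic intracranial hemorrhage definition points the wrong way: it counts a fall of 4 or more points, which the same section calls improvement

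*Protocol article*

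**What the plan says.** Hemorrhage events are a secondary outcome. The abstract of the protocol article lists "Secondary outcomes: neurological function changes, hemorrhage events, cerebral edema" among others, and Section 2.8 (Study outcomes) gives the definitions.

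For change in neurological function, Section 2.8 sets two directions:
- A fall in NIHSS is "classified as improved (postoperative NIHSS score decrease ≥ 4 points compared with preoperative".
- A rise is "worsened (postoperative NIHSS score increase ≥ 4 points compared with preoperative".

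For bleeding, the section first gives the CT grades HI1, HI2, PH1 and PH2. It then adds the symptomatic category: "Symptomatic intracranial hemorrhage was defined as blood at any site in the brain on the CT scan". The list continues with "documentation by the investigator of clinical deterioration, adverse events indicating clinical worsening (e.g., drowsiness, increase of hemiparesis" and ends with "or a decrease in the NIHSS score of 4 or more points". Nothing elsewhere in the article corrects or qualifies that last element.

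**The concern.** The same change in NIHSS serves as a favorable result under one secondary outcome and as a marker of a harmful event under another. Deterioration, a worsening adverse event and increased hemiparesis all describe a patient getting worse. Only the NIHSS element describes a patient getting better.

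The list structure adds a second uncertainty. The elements are separated by commas, with a single alternative before the last. No word ties the CT finding to a clinical element, so the sentence does not settle whether blood on CT is required in every case.

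This matters because the trial sets out to assess both the efficacy and the safety of ECASES. The Introduction gives intracranial hemorrhage as the main risk to weigh against reocclusion when a stent is placed. If recoveries enter the symptomatic count, the comparison of bleeding harm between the arms becomes harder to read and could mislead.

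**Working it through.** **Direction check.** The plan states no figure to reproduce here, so the first step is to set the two rules of Section 2.8 side by side.

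| NIHSS change | Change-in-function outcome | NIHSS element of symptomatic hemorrhage |
|---|---|---|
| Fall of 4 or more | Improved | Met |
| Change of less than 4 | Stable | Not met |
| Rise of 4 or more | Worsened | Not met |

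**The two readings of the list**
- *CT blood required together with a clinical element.* A patient with any blood on CT who improves by 4 or more points counts as symptomatic. A patient with blood whose score rises by 4 or more counts only through documented deterioration or a worsening adverse event.
- *All elements as alternatives.* A patient who improves by 4 or more points counts even with no blood on CT.

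Improved patients are counted under both readings, so the direction error does not depend on how the list is parsed.

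**Who is exposed.** Section 2.2 requires a preoperative NIHSS of at least 6, so every participant has room for a 4-point fall.

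**Size under stated assumptions.** The article gives neither the share of patients with blood on CT nor the share who improve by 4 or more points. Let *b* be the first and *i* the second. Both are assumed values. If they are independent, the share meeting blood plus decrease is *b* × *i*:
- Low end: 0.20 × 0.30 = 6%
- Middle: 0.35 × 0.50 = 17.5%
- High end: 0.45 × 0.60 = 27%

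With 101 patients per arm, the ends are 0.06 × 101 ≈ 6 and 0.27 × 101 ≈ 27 patients per arm.

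Independence is probably generous, since patients who bleed may improve less often. If 35% have blood and only 20% of those improve, the share is 0.35 × 0.20 = 7%.

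**Effect on the comparison between arms.** These are illustrations, again with assumed inputs.
- *Arms recover alike.* Suppose the true rates are 5% and 10%, a ratio of 2.0, and each arm gains 17.5% of falsely counted patients who are separate from the true cases. The observed rates are 22.5% and 27.5%, a ratio of 27.5 / 22.5 = 1.22. A real difference is diluted.
- *Arms recover differently.* Suppose there is no true difference, 35% have blood in each arm, and 50% improve in one arm against 60% in the other. The false counts are 0.35 × 0.50 = 17.5% and 0.35 × 0.60 = 21.0%. The better-recovering arm shows a spurious excess of 3.5 percentage points.

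**The case against.** The best defense is that this is a one-word slip whose intended meaning is plain. The neighboring elements all point to worsening, and experienced staff would probably apply it that way. That is likely true of the intent. It does not rescue the definition: a prespecified outcome should not rely on each evaluator overriding the text, and evaluators may not all do so in the same way.

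Several stronger inferences are tempting and should not be drawn:
- *That symptomatic hemorrhage is defined by the NIHSS fall alone, or that true worsening is lost.* The fall is one of several elements. A bleeding patient who worsens can still count through documented deterioration or an adverse event.
- *That it is the key safety outcome.* The article lists hemorrhage events as one of six secondary outcomes and does not rank them.
- *That any blood on CT is enough, so most patients would be flagged.* With 35% and 50%, the all-alternatives reading gives 1 − (0.65 × 0.50) = 67.5%. Section 2.8 says that events are classified on both clinical and CT grounds, it grades petechial bleeding separately, and the term being defined is symptomatic. CT blood plus a clinical element is therefore the more natural reading, although the sentence does not say so.
- *That the safety signal will be reversed.* This needs arms that differ in early recovery and staff who apply the wording literally. Section 2.11 assumes a good-function rate of at least 51% in both arms. If early recovery is also similar, the result is dilution.
- *That false counts must swamp the true rate.* At the low end of the assumed range, or if bleeding patients seldom improve, they are 6–7%. That lies inside an assumed true rate of 5–10%.

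**Conclusion.** The point holds as an internal contradiction in an outcome definition. Section 2.8 makes a 4-point NIHSS fall both an improvement and an element of symptomatic intracranial hemorrhage, and the wording misclassifies improved patients under either reading of the list. That conclusion needs no assumption.

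The size does need assumptions, because the documents give no rates. About 6–27% of patients would meet blood plus decrease with 20–45% having CT blood and 30–60% improving, independently. The figure is lower if bleeding and improvement seldom go together. Whether the between-arm comparison is merely diluted or shows a false excess depends on whether recovery differs between the arms, which cannot be known in advance.

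The primary outcome, the sample size and the randomization are not affected. The definition should still be corrected before it is used, because it is the rule by which a safety outcome will be counted and it is wrong as written.

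**What to change.** Replace the sentence in Section 2.8 with a two-part rule. Symptomatic intracranial hemorrhage requires blood anywhere in the brain on CT, as judged by the reading panel, AND at least one of:
- clinical deterioration documented by the investigator;
- an adverse event that shows clinical worsening;
- an INCREASE in NIHSS of 4 points or more, in line with the section's own definition of worsened.

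This settles both the direction and the role of the CT finding. Also check that any case report form field for this outcome carries the same wording; the forms are not shown, so there is no evidence either way that they repeat the error.

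The cost is one sentence, plus a form field if it needs changing. No new data are required: Section 2.7 already schedules NIHSS on days 1, 7, 30 and 90 and three CT examinations after surgery.

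### The NIHSS criterion for symptomatic intracranial hemorrhage has the wrong sign: it counts a fall of 4 or more points, which the same section classes as improvement

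*Protocol article*

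**What the plan says.** Hemorrhage is among the secondary outcomes listed in the Abstract: "Secondary outcomes: neurological function changes, hemorrhage events, cerebral edema". Section 2.8 gives the details. It grades hemorrhage on imaging (HI1, HI2, PH1, PH2) and then defines the symptomatic form separately.

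That definition opens with an imaging item: "Symptomatic intracranial hemorrhage was defined as blood at any site in the brain on the CT scan". Clinical items follow in one comma-separated list: deterioration documented by the investigator, then "adverse events indicating clinical worsening (e.g., drowsiness, increase of hemiparesis", and finally "or a decrease in the NIHSS score of 4 or more points".

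Earlier in the same section, the outcome on change in neurological function uses the same scale and the same 4-point threshold. One category is "improved (postoperative NIHSS score decrease ≥ 4 points compared with preoperative"; the opposite category is "worsened (postoperative NIHSS score increase ≥ 4 points compared with preoperative".

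**The concern.** A change on one scale, of one size and in one direction, is recovery in one secondary outcome and evidence of harm in another. Nothing elsewhere in the article reconciles the two.

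The error would not behave like random misclassification. The probability of a false event rises with the probability of recovery, so an arm that does better neurologically can be charged with more symptomatic hemorrhage.

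That matters in this trial. The stated aim covers efficacy and safety, the Introduction names intracranial hemorrhage as the risk set against stenting, and one of the two ECASES risk scores (2.6) is a bleeding score. The criterion is also the item most open to mechanical derivation, because NIHSS is scored on days 1, 7, 30 and 90 (2.7). The data check in 2.9 looks for incorrect entries; it would not detect a wrong rule that had been followed correctly.

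**Working it through.** The article states no figure for this outcome, so there is none to reproduce. The check is a comparison of texts, followed by an illustration of size on assumed rates.

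**Direction of the criterion (2.8)**

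| NIHSS change | Change-in-function outcome | Numeric criterion for symptomatic hemorrhage |
|---|---|---|
| Fall of 4 or more | improved | met |
| Rise of 4 or more | worsened | not met |

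The two columns disagree in both rows. The other clinical items in the definition describe deterioration, so the numeric item also disagrees with its neighbors. Every enrolled patient can meet it by recovering: entry requires "Preoperative National Institutes of Health Stroke Scale (NIHSS) score ≥ 6", and 6 − 4 = 2 is still a possible score.

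**Does the result depend on how the list is joined?**

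- *Blood on CT plus at least one clinical item.* A patient with HI1 petechiae and a 4-point recovery is counted. A patient with blood and a 4-point rise fails the numeric item and is counted only if deterioration or a worsening adverse event is recorded.
- *Any single item qualifies, as the printed list allows.* Every patient in the improved category is counted, with or without blood on CT.

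The sign is wrong under both readings, so settling how the items are joined would not correct it.

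**Size under blood plus one clinical item**

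Assumptions, none of them from the article: h, the proportion with any hemorrhage, is 20-40%; r, the proportion of those patients who improve by 4 or more points, is 20-50%.

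Falsely counted, as a share of all patients, is at most h × r.

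- Low end: 0.20 × 0.20 = 0.04, about 4 of the 101 patients in an arm.
- High end: 0.40 × 0.50 = 0.20, about 20 of 101.

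These are upper bounds at each pair of values, because some of these patients could also qualify correctly on another item.

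For the arm comparison, take equal h in both arms and suppose r is 50% in one and 40% in the other. The spurious difference is at most h × (0.50 − 0.40), which is 0.20 × 0.10 = 2 percentage points to 0.40 × 0.10 = 4 percentage points, against the better-recovering arm.

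**Size under the any-single-item reading, for completeness**

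Use the same h, assume 30-60% of all patients improve by 4 or more points, and assume hemorrhage and recovery are independent. The recorded proportion is then at least 1 − (0.8 × 0.7) = 0.44 to 1 − (0.6 × 0.4) = 0.76. With 50% against 40% improving, the spurious difference is at most 0.6 × 0.10 = 6 to 0.8 × 0.10 = 8 percentage points. These figures combine the sign error with the effect of the *or* list, under which blood alone already qualifies, so they do not measure the sign error by itself.

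**The case against.** The best defense is that this is a one-word slip whose intent is plain. The adjacent items speak of deterioration, and the same section defines worsening as a rise of 4 or more points. Alert staff may apply the intended direction, and neither the case report form nor any derivation code is shown, so nothing proves that the error has gone further. This stands, and it makes the consequence conditional on the rule being applied as written. It does not remove the finding: an operative outcome definition should not depend on staff disregarding its text.

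True cases are also less exposed than false ones. A patient with blood and a 4-point rise can still be caught through documented deterioration or a worsening adverse event. The HI and PH grades do not use NIHSS and are unaffected, as is the primary outcome at 90 days. All of this stands; the main exposure is false positives.

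A reader might infer that the trial's main safety outcome runs backwards. The article does not support that. It lists hemorrhage events as one of several secondary outcomes, symptomatic hemorrhage is one component of them, and only one criterion in that component is reversed. A reader might also take the larger figures from the any-single-item reading as the size of this error. They are not, because much of that recorded proportion comes from blood on CT qualifying alone.

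**Conclusion.** The point holds in a limited form. One criterion for symptomatic intracranial hemorrhage, the only numeric clinical one, contradicts the section's own classification of NIHSS change and the items next to it. This follows from the text alone and needs no assumed rate.

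The size does need assumptions. On the ranges used, up to 4-20% of all patients could be falsely counted under the blood-plus-one-item reading. The upper end takes both extremes together, and the whole range presumes literal application of the rule. The direction of the bias is firmer than its size: false events increase with recovery and tell against the arm that recovers better.

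The correction should be made before the outcome is derived or reviewed by the data and safety monitoring committee. A safety component that can record recovery as harm should not stand when it can be put right so cheaply.

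**What to change.** In 2.8, change *decrease* to *increase* in the NIHSS criterion for symptomatic intracranial hemorrhage, so that it agrees with the section's own worsened category.

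In the same edit, state that blood on CT is required together with at least one of the clinical-worsening items. As printed, the *or* list lets any single item qualify, and changing the one word would leave that open.

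Check the case report form and any derivation rule for the same wording, and correct them if they carry it.

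The cost is a short text edit and a check of two documents. No patients, visits, procedures or treatment decisions change.
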